**Methods:**

The study will be run as a randomized controlled trial with a 6-month duration in Portugal. Eligible participants will be randomized using a 1:1 ratio for intervention or control groups and compared using an intention-to-treat analysis. The intervention will consist of a walking football exercise program. The control group will continue with usual care in primary health care units. The primary outcome will be the mean difference in glycated hemoglobin between intervention and control groups after 6 months. Secondary outcomes include the mean differences in fasting blood glucose, total cholesterol, low-density lipoprotein cholesterol, high-density lipoprotein cholesterol, triglycerides, systolic and diastolic blood pressure, body mass index, waist circumference, fat-free mass, and fat mass. Additionally, secondary outcomes include the incidence of exercise-related injuries and adverse events and the walking football exercise program’s cost-utility.

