### Data Analysis and Sample Size

The number of participants to be involved was defined to test the superiority of walking football compared with usual care, using intention-to-treat analysis. For a 1:1 ratio of the intervention and control groups, significance level of 5%, and statistical power of 80%, a total of 162 participants will be needed to detect a mean difference of at least 0.35% in the primary outcome (glycated hemoglobin), based on previous meta-analyses [33,34]. Assuming the complete follow-up of at least 80% of the participants, a total of 200 participants will be enrolled.

We will use a 2-way (group*time) analysis of variance with repeated measures to compare the mean differences between intervention and control groups.

For the cost-utility analysis, we will calculate the walking football implementation costs compared with the usual care. Costs include technical training for the professionals involved, patients’ medical assessments, material for capillary blood glucose and blood pressure evaluations, football equipment, sports facility rental, sports insurance, and payment to nurses and football coaches. The costs of the intervention and reported gains in quality of life (based on quality-adjusted life years) [27] will be used to calculate the incremental cost-utility ratio (ICUR). ICUR will be compared with the World Health Organization thresholds for health interventions based on per capita gross domestic product.

The amount of missing data is expected to be low considering the training of all the staff and the use of standardized procedures for data collection. No imputation is being planned.

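### The analysis is called intention-to-treat, but a two-time-point repeated-measures ANOVA with no imputation becomes a complete-case analysis at the 20% loss allowed for

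*Protocol article*

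**What the plan says.** The abstract's Methods paragraph says the groups will be "compared using an intention-to-treat analysis". Data Analysis and Sample Size repeats this: the trial was sized "to test the superiority of walking football compared with usual care, using intention-to-treat analysis". That section names a two-way (group by time) repeated-measures ANOVA as the analysis. It arrives at 162 participants and then inflates: "Assuming the complete follow-up of at least 80% of the participants, a total of 200 participants will be enrolled".

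Its last paragraph deals with missing data in two sentences. "The amount of missing data is expected to be low considering the training of all the staff", with standardised collection procedures given as a further reason, and then "No imputation is being planned".

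Three other sections bear on this. Data Collection places the HbA1c measurements at baseline and 6 months only. Intervention and Control Groups sets 72 supervised sessions over 24 weeks for one arm. Assignment of Interventions says blinding is not possible, and Ethics and Dissemination lets participants withdraw at any time. Limitations discusses blinding and contamination but not attrition.

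**The concern.** The section makes three commitments that do not fit together once men are lost: an intention-to-treat claim, a model that needs both HbA1c values from each man, and a ruling against imputation. The trial is sized to tolerate the loss of one man in five, so this is a situation the plan itself provides for.

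The rationale for expecting few missing values does not close the gap. Training and standard procedures limit recording errors and missed measurements among men who attend their assessments. They do little about men who leave. The burden of the programme falls on one arm, and everyone knows the allocation, so loss that differs between arms in amount or in kind is plausible.

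At stake is the primary estimate. It would rest on an unstated assumption about dropout while carrying a label that suggests no such assumption is needed.

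**Working it through.** **1. The plan's own figures.** Inputs from Data Analysis and Sample Size: difference 0.35, alpha 5% (taken as two-sided), power 80%, 1:1 allocation, 162 in total (81 per arm), at least 80% follow-up, 200 enrolled.

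- Inflation: 162 / 0.80 = 202.5, rounded up to 203, against 200 stated. The gap is trivial.
- Men analysed at the full allowance: 200 × 0.80 = 160, so 40 are left out.
- No SD is stated. Solving backwards: SD = 0.35 × √(81/2) / (1.960 + 0.842) = 0.795. At 80 per arm this gives 79.5% power.

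The sample size is therefore not at issue.

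**2. What the planned test does with a missing 6-month value.** With two time points, the group-by-time F statistic equals the squared two-sample t statistic on the change from baseline. In one simulated data set both came to 9.38. A man without a 6-month HbA1c has no change score and contributes nothing.

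**3. Size of the bias by arithmetic.** If a fraction p of an arm is lost and the lost men's mean change is worse than the completers' by a gap g, the completers' mean differs from the whole arm's mean by p × g. The gaps below are assumptions.

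- Intervention arm 20% lost, g from 0.20 to 0.80, control loss uninformative: 0.20 × 0.20 = 0.04 up to 0.20 × 0.80 = 0.16. Relative to 0.35 that is 11% to 46%, in favour of walking football.
- Same gap in both arms with equal loss: the bias cancels.
- Same gap in both arms with loss split 30% and 10%: (0.30 - 0.10) × g, again 0.04 to 0.16.

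**4. Dropout that depends on baseline HbA1c.** Assumptions: true effect -0.35, baseline SD 1.0, intervention-arm dropout with log-odds 0.8 per SD of baseline. The change-score analysis of completers gives about -0.30. The same men analysed with baseline adjustment give -0.35. Varying the baseline SD from 0.9 to 1.0 and the correlation between the two measurements from 0.5 to 0.7 moves the change-score estimate between -0.28 and -0.32. Here the planned analysis understates the effect.

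**5. Dropout that depends on the outcome, under no true effect.** Assumptions: 100 per arm, SD of change 0.795, 20% loss in each arm, intervention-arm dropout with log-odds 0.5 or 1.0 per SD of worse change. Ranges cover repeated simulations. The baseline-adjusted row also assumes a baseline SD of 1.0 and a slope of change on baseline of -0.3.

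| Dropout pattern | Bias at 0.5 / 1.0 | Rejection at 0.5 / 1.0 |
|---|---|---|
| Unrelated to outcome | about 0 | about 5% |
| Intervention arm only | -0.07 to -0.08 / -0.14 | 8–10% / 20–21% |
| Control slope half the intervention's | -0.03 to -0.04 / -0.06 | 6% / 7.5–8% |
| Same slope in both arms | about 0 | 4–5% |
| Intervention arm only, baseline-adjusted | -0.07 / -0.12 | 7–9% / 18% |

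If intervention-arm loss is allowed to drift to about 24%, the strong one-arm case reaches 26%, but that exceeds the plan's allowance.

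**The case against.** Several points on the other side are sound.

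- **The 80% figure is a planning floor, not a forecast.** Forty men is the most the plan allows for, across both arms. The sentence about low missingness can also be read as describing data capture among men who attend. This softens the tension between the two statements but does not remove it, because nothing then covers the men who do not attend.
- **Silence is not evidence.** A reader might infer that the trial has no check at all on dropout bias. The documents do not support that: this is a condensed article, and an SAP could add sensitivity analyses. What is stated, and not merely left out, is the model and the ruling against imputation.
- **Stopping sessions is not the same as missing the blood test.** A reader might infer that every man who leaves the programme leaves the analysis. Nothing in the article ties the 6-month measurement to attendance. A man who stops playing but is measured stays in his allocated arm, as intention-to-treat requires.
- **The large simulated errors come from a one-arm worst case.** With half the slope in controls, rejection is only 6 to 8%. With equal slopes and equal loss there is no inflation.
- **A better primary model does not cure outcome-related dropout.** The last row of the table shows this. In the baseline-dependent case, adjustment for baseline among completers is already enough to remove the bias. The likelihood-based model draws on the same information and makes its assumption explicit.

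What remains is that the label, the model and the missing-data rule conflict as written.

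**Conclusion.** The point holds in a limited form. At the loss the plan allows for, the analysis called intention-to-treat is a change-score comparison of about 160 completers, with up to 40 randomised men left out. This follows from stated rules and needs no assumption beyond the allowed loss occurring.

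Bias is a risk and not a certainty, and it can run either way. The baseline-dependent illustration dilutes the effect by about 0.05 (0.35 - 0.30). The one-arm outcome-dependent worst case produces a spurious benefit of 0.07 to 0.14 and a type I error of roughly 8 to 20%. Both rest on assumed dropout mechanisms, and the second also on an SD solved back from the sample size. The documents do not show that dropout will behave in either way.

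**What to change.** In Data Analysis and Sample Size, replace "No imputation is being planned" and the low-missingness rationale with three statements:

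1. **Primary analysis.** All randomised men are analysed in their allocated group with a likelihood-based longitudinal model that has baseline and 6-month HbA1c as responses and a common baseline mean. Multiple imputation by arm is an acceptable alternative. State that this assumes data are missing at random given what is observed.
2. **One prespecified sensitivity analysis.** Use either delta-adjusted or control-based imputation for men without a 6-month HbA1c. This is the part that addresses outcome-related dropout.
3. **Data collection.** The planned 6-month HbA1c is sought from men who stop attending sessions but have not withdrawn consent.

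Two additions are best avoided. Session attendance is recorded only in the intervention arm, so it cannot serve as an imputation predictor for controls. Mandatory substitution of routine primary-care HbA1c values would raise questions of consent, timing and assay.

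The cost is a little extra analysis work, some effort to bring back men who stopped attending, and possibly a slightly less favourable estimate. No sample-size figure changes. The article's Results section says recruitment will follow ethics approval, so the change can be made before any outcome is seen.

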### Ethics and Dissemination

This study will follow the General Data Protection Regulation and be submitted to the Health Ethics Committee of the Northern Regional Health Administration, Portugal. All procedures will comply with the Declaration of Helsinki. Any protocol deviation will be reported.

All participants will provide informed consent after receiving a detailed explanation of the potential risks and benefits. They will also have research insurance to cover the risks associated with exercise practice and evaluations before and after the exercise program. All participants will have a codification number to be used in the evaluations (questionnaires and blood samples). All the data collected will be treated as confidential and strictly used for this project. Data storage will be anonymized. Only the principal investigator will have access to the data.

Participants can withdraw from the study at any time, without any prejudice to the care provided at their PHCU, and have the right to access personal data collected in person from the researchers.

Findings from this study will be submitted for publication in international peer-reviewed journals. The results will also be disseminated at national and international scientific meetings and in mass media press releases.

## Results

The study protocol is being prepared to be submitted to the Health Ethics Committee of the Northern Regional Health Administration, Portugal. After approval, participant recruitment will start by family medical doctors in PHCUs in Porto’s metropolitan area.

## Discussion

### Overview

The main goal of this study is to test the effectiveness of a walking football program for glycemic control and cardiovascular risk factors in middle-aged and older male patients with T2D.

To the best of our knowledge, this is the first study testing the effects of a walking football exercise program for these outcomes in this specific population. Also, the investigation proposed relies on robust methodology, with a large study sample.

We expect that the walking football program will be effective in improving diabetes control and cardiovascular risk factors. We also expect a low rate of exercise-related injuries and adverse events and a good cost-utility ratio, as observed in other studies testing the effect of physical activity on diabetes control [35-38].

Developing an effective program with a good cost-utility ratio may contribute to making walking football a sustainable intervention strategy for T2D control. In addition, it can be used by football clubs to offer these programs as a service to their communities, ultimately contributing to the sustainability of the intervention and scaling up the offer to population coverage.

### Limitations

Some limitations need to be addressed: First, the lack of participant, health care professional, and elements of the research team’s blinding may introduce bias that may affect the outcome assessment. Nevertheless, our primary outcome is an objective measure — glycated hemoglobin, measured by blood clinical analysis — which may reduce the impact on the lack of blinding.

Second, contamination may occur since randomization units are individuals and not PHCUs, and there is proximity in the geographical area for participants from each PHCU. However, education of all research members and participants towards contamination and clear information about the purposes of the trial may minimize its occurrence.

## Appendix

Multimedia Appendix 1 The Standard Protocol Items: Recommendations for Interventional Trials checklist.

## Abbreviations

HR: heart rate
HRR: heart rate reserve
ICUR: incremental cost-utility ratio
PHCU: primary health care unit
RPE: rating of perceived exertion
SPIRIT: Standard Protocol Items: Recommendations for Interventional Trials
T2D: type 2 diabetes
